**Fig. 2 Fig2:**
[figure not shown]
Levator ani muscle SWE assessment: probe position and example of acquisition

The woman’s position will be the same as for the levator ani muscle. We will place the probe on the perineum immediately above the anus in the axial plane (Fig. 3). We will first locate the external muscle using a B-mode ultrasound and then proceed to the SWE assessments in the middle of the anterior zenith of the sphincter ring for the three conditions: rest, maximal Valsalva maneuver and subjective maximal perineal contraction [33].
Specificity for biceps brachii muscle assessment

**Fig. 3 Fig3:**
[figure not shown]
External anal sphincter SWE assessment: probe position and example of acquisition

First, we will identify the proximal and distal insertion of the biceps brachii using B-mode ultrasound and perform SWE acquisition midway between these insertions for three conditions: rest, standardized extension, and subjective maximal contraction. We will perform an assessment at rest performed with the upper limb having a 90° flexion of the elbow, which will be at the same height as the shoulder, with the hand in the pronation position. The forearm will rest on a flat support, allowing the *biceps brachii* to be totally free and accessible (Fig. 4A). We will systematically verify the 90° flexion of the elbow using a digital goniometer. For the assessment during extension, the position will be the same but with a 180° extension of the elbow (verified with the digital goniometer) and the hand in the pronation position (Fig. 4b). Finally, for the measurements during contraction, we will ask the woman to have a subjective maximal contraction of her *biceps brachii* in the rest assessment position. With this procedure, a previous study reported that the shear modulus measured in *biceps brachii* muscle in non pregnant volunteer is about 3 kPa at rest and 19 kPa when stretched [25, 34].
Specificity for gastrocnemius medialis muscle assessment

**Fig. 4 Fig4:**
[figure not shown]
SWE acquisitions of the *biceps brachii* muscle at rest and standardized extension

Usually, this measure is performed with the volunteer lying down in ventral decubitus. Because of the evident risks of compression of the gravid uterus, such a position is not ideal for pregnant women, and so the assessments will be performed while the woman is in left lateral decubitus. First, we will identify the proximal and distal insertions as well as the lateral borders of the *gastrocnemius medialis* in B-mode ultrasound. We will perform the SWE acquisition midway between the lateral borders and midway between the proximal and distal insertions of the muscle for the three conditions: rest, standardized extension, and subjective maximal contraction. For the assessment at rest, the left leg will be flexed, the right leg will be fully extended (180°, verified with the digital goniometer) and the ankle will be in a neutral position (Fig. 5a). For the measurement during extension, the woman will be in the same position but with the right foot supported on a 20° inclined plane to apply a standardized extension of the *gastrocnemius medialis* (Fig. 5b). Finally, we will proceed to obtain the measurement during contraction with the woman in the same position as for the assessment at rest but with a voluntary maximal contraction of the *gastrocnemius medialis.* With this procedure, a previous study reported that the shear modulus measured in *gastrocnemius medialis* muscle in non pregnant volunteer is about 3.1 kPa at rest [25].
*Data related to mode of delivery*

**Fig. 5 Fig5:**
[figure not shown]
SWE acquisitions of the *gastrocnemius medialis* muscle at rest and standardized extension

After childbirth, we will obtain the following data from the subjects’ medical files:
spontaneous or induced laborepidural analgesiaduration of the second stage of labor (time between full cervical dilatation and the birth, in minutes)duration of the expulsive phase (time between the onset of pushing and the birth, in minutes)mode of delivery (spontaneous vaginal delivery, operative vaginal delivery, cesarean delivery)indication for potential cesarean delivery (fetal distress, other)type of instrument used for potential operative delivery (vacuum, forceps, spatulas)indication for potential operative delivery (fetal distress, other)episiotomy usepotential perineal tears classified according to the Royal College of Obstetricians and Gynaecologists (RCOG) guidelines [35, 36].

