### Population

The inclusion criteria are as follows: women older than 18 years, volunteers, nulliparous, with a normal singleton pregnancy, and who benefit from health insurance.

The exclusion criteria are as follows: women with previous vaginal and/or cesarean delivery, women with a personal history of pelvic floor disorders (urinary incontinence, anal incontinence, pelvic organ prolapse), women with a body mass index (BMI) higher than 35 kg.m^− 2^, women with chronic muscular disease, women requiring admission into a psychiatric unit, women under judicial protection, and women unable to understand the French language.

If an included woman has a pregnancy who became pathological (define by the necessity of follow-up into pathological pregnancies consultations and/or admission in pathological pregnancies unit) she will no longer participate to the study and no data will be collected after this event. If a woman wants to stop its participation, no more data will be collected.

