#### Plan of analysis

We will describe the anthropometric and sociodemographic characteristics of the included women. Age, BMI and term of pregnancy will be reported as the mean and standard deviation (SD). For all the other analysis, we will only consider data about women who completed the three planned visits. For each trimester, we will only collect continuous variables, which will be reported as the means and SDs. Changes in these variables during pregnancy will be investigated using a Friedman test. Obstetric data will be reported as the means and SD for continuous variables and as percentages and frequencies for categorical variables.

Regarding the study endpoints, we will first report the main outcome of this study, which consists of the changes in the pelvic floor muscle’s shear modulus across the pregnancy. Then, we will report the changes in all other measured pelvic floor-related parameters (POP-Q measurements, ultrasound B-mode measurements). We will look for an association between the shear modulus of the levator ani muscle and clinical (POP-Q measurements) and ultrasound B-mode assessments at each trimester using a Spearman correlation coefficient calculation. Second, we will report the changes in the shear modulus of the *biceps brachii* and *gastrocnemius medialis* muscles to look for changes between the different investigated locations. Third, we will look for an association between the shear modulus of the pelvic floor muscles (*levator ani* and external anal sphincter) and both the mode of delivery (vaginal or cesarean delivery) and perineal tear occurrence using univariate analysis. Variables with a level of significance greater than *p* < 0.15 in univariate analysis will be included in the multivariate analysis using a logistic regression. We will perform statistical analysis with Stata software (version V14IC; Stata Corporation, College Station, TX, USA). For all analyses, significance will be considered for *p* < 0.05, and we will calculate odds ratios (ORs) with 95% confidence intervals when appropriate.

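### The vaginal-versus-cesarean comparison counts prelabor cesareans as events, and the delivery coding cannot reliably separate them from cesareans for first-stage arrest (minor)

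*Protocol article*

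**What the plan says.** In Methods, Data collection, the list of data related to mode of delivery gives several items with their levels. Onset of labor is either spontaneous or induced. Mode has three levels: "mode of delivery (spontaneous vaginal delivery, operative vaginal delivery, cesarean delivery". The reason for a cesarean is recorded as "indication for potential cesarean delivery (fetal distress, other". The list also includes the durations of the second stage and of the expulsive phase.

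The last secondary criterion under Judgment criteria links pelvic floor shear modulus at the last visit to mode of delivery (three levels) and to perineal tears. Plan of analysis reduces mode to two levels and will relate modulus to "both the mode of delivery (vaginal or cesarean delivery) and perineal tear occurrence using univariate analysis". For everything after the description of the sample, "we will only consider data about women who completed the three planned visits". The comparison is not limited to women who labored, and the cesarean indication is given no role in it.

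Two rules under Population bear on how many prelabor cesareans can occur. The exclusions include "women with previous vaginal and/or cesarean delivery". When a pregnancy becomes pathological, "she will no longer participate to the study and no data will be collected after this event".

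**The concern.** A woman delivered by cesarean before labor never tests her pelvic floor against the birth. Her modulus cannot have influenced the mode of delivery through the course of labor. Counted with the cesareans, she adds an event that carries no information on that question and pulls the vaginal-versus-cesarean difference toward zero.

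The pooling comes from the two-level comparison in Plan of analysis. The coding matters because it limits what can be repaired afterwards. With no level for absent labor, and with arrest of labor folded into the residual indication, the analyst lacks the fields needed to take prelabor cesareans out cleanly. At stake is the meaning of one reported association: a small observed difference could reflect no relation, or a relation diluted by births to which it could not apply.

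**Working it through.** **Can the coding separate the cases?** Applying the levels in the delivery data list as written:

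| Birth | Labor onset | Mode | Indication | Second-stage duration |
|---|---|---|---|---|
| Cesarean before labor, not for fetal distress | no level fits | cesarean | other | none |
| Cesarean for arrest before full dilatation | spontaneous or induced | cesarean | other | none |
| Cesarean for arrest after full dilatation | spontaneous or induced | cesarean | other | present |
| Cesarean in labor for fetal distress | spontaneous or induced | cesarean | fetal distress | depends on stage |

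The third row can be identified by its second-stage duration and the fourth by its indication. The first two rows differ only in labor onset, the item with no level for the first row. A blank there could mean no labor or a missing entry, and the article gives no rule for reading it.

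**Can prelabor cesareans reach the analysis?** Excluding women with a previous cesarean removes repeat operations. The withdrawal rule removes some planned cesareans, but its trigger is follow-up in a pathological-pregnancy consultation or unit, not a plan for cesarean. The last visit is at 34–38 weeks, so a woman can complete all three visits and then have a cesarean before labor. The number is reduced but not shown to be zero.

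**How much does pooling dilute the comparison?** The plan has no figure to reproduce here: Power calculation gives no power computation, and nothing is stated for mode of delivery. Let D be the mean modulus difference between cesareans in labor and vaginal births, and f the share of all cesareans that are prelabor. Suppose prelabor cesareans have the same mean modulus as vaginal births. Then

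pooled difference = (1 − f) × D + f × 0 = (1 − f) × D

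| f (assumed) | Pooled difference as a share of D |
|---|---|
| 10% | 0.90 |
| 20% | 0.80 |
| 35% | 0.65 |
| 50% | 0.50 |

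**Check on the supposition.** If D is not zero, prelabor cesareans may instead resemble all women who labored, whose mean lies slightly toward the cesarean side. With p the share of cesareans among women who labored, the factor becomes 1 − f × (1 − p). Take 50 completers (the protocol's target) and an assumed 10 cesareans:

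- f = 10%: 1 prelabor, 9 of 49 labored women with cesarean, p = 9/49 = 0.18; factor = 1 − 0.10 × 0.82 = 0.92.
- f = 50%: 5 prelabor, 5 of 45 labored women with cesarean, p = 5/45 = 0.11; factor = 1 − 0.50 × 0.89 = 0.56.

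These are close to 0.90 and 0.50, so (1 − f) serves as an approximation. At 10 cesareans the range of f corresponds to between 1 and 5 women.

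**The case against.** The strongest reply is that little depends on this comparison. The study is exploratory, mode of delivery is not named in the stated objectives, and the Discussion says the sample will not allow a conclusion on these associations. That stands, and it is why the point is minor.

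A second reply is that a published article condenses the case report form, and that the medical files could show whether a woman labored. This stands in part: the source files could settle the matter. But the article itself states the levels and the two-level comparison, and following them as written gives the mixing described above.

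A third reply is that the plan speaks only of an association and states no causal hypothesis about stiffness and cesarean. That is correct. Restricting to women who labored makes the association easier to interpret; it does not repair a broken test.

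Several stronger readings are tempting but not supported:

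- *That the larger study would be planned on a diluted estimate.* The Discussion ties the preliminary data and the future study to perineal tears and the prediction of perineal trauma, not to cesarean.
- *That no cesareans can be told apart.* Those after full dilatation can be, by second-stage duration, and those for fetal distress can be, by indication.
- *That the matching item "indication for potential operative delivery (fetal distress, other" distorts the same comparison.* Operative vaginal births count as vaginal there, so their indication cannot affect it.
- *That a definite loss of power can be stated, or that the full difference returns once prelabor cesareans are removed.* Either needs an assumed cesarean rate, effect and test (the plan says only that the analysis is univariate). It also needs cesareans for fetal distress to carry the same effect as those for arrest. If they do not, they dilute the comparison even among women who labored.

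**Conclusion.** The point holds as a minor one. As written, the plan counts any prelabor cesarean as a cesarean event in the modulus comparison, and its coding does not reliably distinguish such a birth from a cesarean for first-stage arrest. The observed difference would be about (1 − f) of that in women who labored, from 0.9 at f = 10% to 0.5 at f = 50%.

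This size rests on two assumptions: the range of f, for which the documents give no basis, and prelabor cesareans having about the same mean modulus as vaginal births. The Population rules favor the lower part of the range without fixing it. With no prelabor cesareans among completers there is no dilution. The primary endpoint, the change in shear modulus across pregnancy, is untouched, and so are the tear-based data meant for the larger study.

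**What to change.** In the delivery data list, record labor onset as spontaneous, induced or none, and cesarean indication as fetal distress, arrest of labor or other.

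In Plan of analysis, run the vaginal-versus-cesarean comparison in women who labored, describe prelabor cesareans separately, and describe shear modulus by cesarean indication. The last step matters because cesareans for fetal distress remain in the restricted comparison and may differ from those for arrest.

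The cost is two extra code levels, read from medical files already being opened, and a sentence or two in the plan. No extra visit is needed. The downside is a few fewer women in an exploratory comparison.

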### Analysis

#### Judgment criteria

The primary judgment criteria will be the evolution of the shear modulus of the pelvic floor muscle (*levator ani* and external anal sphincter) across the pregnancy assessed at rest, during the Valsalva, and during a contraction.

Secondary judgment criteria will be:
the association between POP-Q measurements (especially gh and pb) and the elastic properties (shear modulus) of the levator ani muscle at each visit;the association between perineal B-mode ultrasound measurements and the elastic properties (shear modulus) of the levator ani muscle at each visit;the changes in shear modulus of the *biceps brachii* and *gastrocnemius medialis* muscles during pregnancy compared to the pelvic floor muscles;the association among the shear modulus of the pelvic floor muscles (*levator ani* and external anal sphincter) at the last visit, the mode of delivery (spontaneous vaginal delivery, operative vaginal delivery, cesarean delivery) and the potential occurrence of a perineal tear (RCOG-WHO classification, French guidelines) [35, 36].

#### Plan of analysis

We will describe the anthropometric and sociodemographic characteristics of the included women. Age, BMI and term of pregnancy will be reported as the mean and standard deviation (SD). For all the other analysis, we will only consider data about women who completed the three planned visits. For each trimester, we will only collect continuous variables, which will be reported as the means and SDs. Changes in these variables during pregnancy will be investigated using a Friedman test. Obstetric data will be reported as the means and SD for continuous variables and as percentages and frequencies for categorical variables.

Regarding the study endpoints, we will first report the main outcome of this study, which consists of the changes in the pelvic floor muscle’s shear modulus across the pregnancy. Then, we will report the changes in all other measured pelvic floor-related parameters (POP-Q measurements, ultrasound B-mode measurements). We will look for an association between the shear modulus of the levator ani muscle and clinical (POP-Q measurements) and ultrasound B-mode assessments at each trimester using a Spearman correlation coefficient calculation. Second, we will report the changes in the shear modulus of the *biceps brachii* and *gastrocnemius medialis* muscles to look for changes between the different investigated locations. Third, we will look for an association between the shear modulus of the pelvic floor muscles (*levator ani* and external anal sphincter) and both the mode of delivery (vaginal or cesarean delivery) and perineal tear occurrence using univariate analysis. Variables with a level of significance greater than *p* < 0.15 in univariate analysis will be included in the multivariate analysis using a logistic regression. We will perform statistical analysis with Stata software (version V14IC; Stata Corporation, College Station, TX, USA). For all analyses, significance will be considered for *p* < 0.05, and we will calculate odds ratios (ORs) with 95% confidence intervals when appropriate.

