## Methods

### Design

The ELASTOPELV study will be a prospective, longitudinal, monocentric study. The scheme of the study will involve 3 visits during pregnancy: the first one between 14 and 18 weeks, the second between 24 and 28 weeks and the last between 34 and 38 weeks of pregnancy (Fig. 1). For each of these three visits, the protocol will follow these steps: clinical perineal assessment, ultrasound B-mode perineal assessment, SWE assessment of the *levator ani* muscle, the external anal sphincter, the *biceps brachii* muscle and the *gastrocnemius medialis* muscle (Fig. 1).

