### Power calculation

This study deals with exploratory data with an absence of previous data that would allow a power calculation. Furthermore, the main endpoint of the project is descriptive (to describe changes in the elastic properties of the *levator ani* muscle during pregnancy), and, therefore, an a priori power calculation does not appear necessary. We aim to obtain and study the data from at least 50 women. We considered this sample size in part due to previous studies that reported an increase in *levator hiatus* area and ligamentous laxity during pregnancy, as well as changes in the intrinsic biomechanical characteristics of pregnant women, from between 20 to 50 women [17–19]. We estimate that 20% of the women will be excluded during pregnancy because of a complicated pregnancy and/or their own choice, leading to an objective of 60 inclusions.

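### Limiting the analyses to three-visit completers and testing change only with a Friedman test discards collected visits and leaves the change, the main objective, without a planned confidence interval

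*Protocol article*

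**What the plan says.** The Plan of analysis opens with all recruits: "We will describe the anthropometric and sociodemographic characteristics of the included women". Everything else is restricted: "For all the other analysis, we will only consider data about women who completed the three planned visits". The visit summaries are specified as follows: "For each trimester, we will only collect continuous variables, which will be reported as the means and SDs". The test follows: "Changes in these variables during pregnancy will be investigated using a Friedman test". Confidence intervals are mentioned once, with the logistic regression output: "we will calculate odds ratios (ORs) with 95% confidence intervals when appropriate". Spearman correlations between levator ani shear modulus and the clinical and B-mode measures are planned separately for each trimester.

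On losses, the Power calculation section states: "We estimate that 20% of the women will be excluded during pregnancy". It gives complicated pregnancy and the woman's own choice as reasons, without a split. The Population section stops data collection when a pregnancy becomes pathological or a woman withdraws, so visits before that point are already on file. The Design section sets the visit windows: "the first one between 14 and 18 weeks, the second between 24 and 28 weeks and the last between 34 and 38 weeks" of pregnancy. The main endpoint is called descriptive, and the Expected results section anticipates a rise in stiffness.

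**The concern.** Three features fit poorly with a study whose purpose is to describe change.

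- **Valid visits are dropped.** A woman who leaves after visit 1 or 2 was measured while her pregnancy was normal. The completer rule removes those measurements even from analyses that need no later visit, such as the visit 1 correlations.
- **Those who stay may differ.** Some losses come from complicated pregnancy. If leaving is related to earlier shear modulus values, completers do not represent the women recruited.
- **The named test does not describe.** A Friedman test gives a p-value. Its statistic is unchanged if the three visits are relabelled, so it does not use their order, and it cannot take in the actual gestational week. The size of the change and its precision are what a descriptive study should deliver. The Discussion also hopes the data will support a power calculation for a later study.

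**Working it through.** **1. Expected numbers (Power calculation section).** Adding 20% to the target of at least 50 gives 50 × 1.20 = 60, the planned inclusions. Applying the loss forward gives 60 × 0.80 = 48 completers and 12 leavers. (Dividing by 0.8 would give 62.5, so 63; that is a separate point.)

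**2. Precision lost by dropping the 12 leavers.** The documents give no SD or within-woman correlation ρ. I assume equal variances, one common ρ from 0.2 to 0.8, and that all 12 made at least visit 1. The ratio below is the variance using all recorded visits divided by the variance using completers only.

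- All 12 leave after visit 1. For the visit 1 to 3 change (and equally visit 1 to 2), the all-visit variance is (1−ρ²)/48 + (1−ρ)²/60 and the completer variance is 2(1−ρ)/48. The ratio is 0.9 + 0.1ρ, from 0.92 at ρ = 0.2 to 0.98 at ρ = 0.8.
- All 12 leave after visit 2. For visit 1 to 2 the ratio is 48/60 = 0.80 at any ρ. For visit 1 to 3 it runs from 0.917 (ρ = 0.2) to 0.944 (ρ = 0.8).
- Six leave at each point. The ratios are 0.918 to 0.960 for visit 1 to 3 and 0.853 to 0.880 for visit 1 to 2.

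The saving is therefore about 2-8% of the variance for visit 1 to 3 and 2-20% for visit 1 to 2.

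**3. Visit 1 correlations.** The Fisher-z standard error is proportional to 1/√(n−3). Using 48 women rather than 60 multiplies it by √(57/45) = 1.125, about 13%.

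**4. What the visit means and SDs leave out.** In completers, the difference between two visit means equals the mean within-woman change, so its size and direction can be read off. Its precision cannot. With a common SD, the SD of the change is SD × √(2(1−ρ)), which is 1.26 SD at ρ = 0.2 and 0.63 SD at ρ = 0.8. With 48 women the standard error is 0.18 SD or 0.09 SD, a twofold range that the planned summaries do not resolve.

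**5. Efficiency of the Friedman test.** The Design section fixes k = 3: "The scheme of the study will involve 3 visits during pregnancy". With normal errors, the asymptotic efficiency relative to the repeated-measures F test is 3k/(π(k+1)) = 9/(4π) = 0.716, so 48 women act like 48 × 0.716 = 34.4. This depends on the distribution:

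| Error distribution | Efficiency |
|---|---|
| Lower bound | 0.648 |
| Normal | 0.716 |
| Uniform | 0.75 |
| Lognormal, log-SD 0.25 | 0.81 |
| Logistic | 0.82 |
| Laplace | 1.125 |
| Lognormal, log-SD 0.5 | 1.18 |

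Simulated power at n = 48 (4,000 runs per setting) for an assumed linear rise of 0.6 within-woman SD from visit 1 to 3, Friedman against F: normal errors 0.60 against 0.75; lognormal (log-SD 0.5) 0.79 against 0.74; t with 3 degrees of freedom 0.87 against 0.78. With normal errors and rises of 0.5 and 0.7 SD, the pairs are 0.45 against 0.58 and 0.75 against 0.87.

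**6. Time between visits.** The windows allow 24 − 18 = 6 to 28 − 14 = 14 weeks between visits 1 and 2, and 34 − 18 = 16 to 38 − 14 = 24 weeks between visits 1 and 3. These are extremes. The windows do not overlap, and their midpoints are 10 weeks apart.

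**The case against.** The Friedman test is a valid test with few assumptions for three repeated measures in about 48 women, and in an exploratory study power is secondary. The data recovered from leavers are few. Women who leave before visit 3 could not enter the delivery and tear analysis under any method, because it uses shear modulus at the last visit. The study concerns normal pregnancy, so completers are an arguable target population; a mixed model would implicitly carry the leavers' course forward as if it had continued. A condensed article need not list every interval.

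Much of this stands. It also rules out stronger readings that a reader might infer:

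- *Every analysis is restricted.* The description of included women is not.
- *The plan gives no estimate of change.* Visit means in the same women give one; its interval is what is missing.
- *The plan loses about 28% efficiency.* That figure (1 − 0.716) needs normal errors, which the documents do not establish. It belongs to the Friedman test and not to the completer rule, and it can reverse.
- *Women leave mainly because of complications, so the result is biased.* The article gives no split of reasons and nothing that links leaving to shear modulus.

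The defence is incomplete on two counts. The article does not give pregnancies that stay normal as its reason for the completer rule, and that reason would not cover women who leave by choice. The completer rule and the Friedman test are also stated outright, not left to another document.

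**Conclusion.** The point holds as a moderate one. Following the article as written discards collected visits from about 12 of 60 women and names no interval for the within-woman change, the quantity of main interest. That the test ignores visit order and gestational week does not depend on the error distribution.

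The precision cost is modest: about 2-8% of variance for the visit 1 to 3 change, 2-20% for visit 1 to 2, and a standard error about 13% larger for the visit 1 correlations. These figures rest on the plan's 20% loss, and the two variance ranges also on an assumed common correlation of 0.2 to 0.8. Selection bias is a risk that the documents neither show nor exclude. The Friedman test's efficiency of about 72% applies only if errors are normal; with skewed or heavy-tailed values the loss can vanish or reverse.

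**What to change.** - Make the main analysis a linear mixed model of log shear modulus on all recorded visits of all included women, with a random effect for woman and visit as a categorical time variable. Report the percentage change between visits with 95% confidence intervals. Add a supporting analysis with actual gestational week as the time variable.
- For the Spearman correlations, use every woman measured at the visit concerned.
- Keep the Friedman test in three-visit completers as a sensitivity analysis.

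The cost is analysis-plan wording and analysis work; no extra women or measurements are needed. The model assumes roughly normal log values and missing visits explained by the observed ones. It describes all included women and not only pregnancies that stayed normal. If the latter is the intended population, the plan should say so and give the reason.
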